#### Cognitive Function

The short screening tool Montreal Cognitive Assessment (MoCA) will be used to evaluate the participants’ cognitive functions (eg, memory, attention, and basic functions). Participants who achieve a MoCA score between 26 and 30 points will be classified as cognitively healthy; those with a MoCA score of 19-25 will be considered to have mild cognitive impairment; and participants with a MoCA score of less than 19 will be defined as severely cognitively impaired [58].

#### Psychosocial Health

Psychosocial health outcomes will be assessed using modified, validated, and reliable instruments included in a self-administered questionnaire. Thus, the psychological and social domains of the Tilburg Frailty Indicator [59], the German depression scale for older adults, namely Depression im Alter Skala [60], and modified items of the Fragebogen zur sozialen Unterstützung (social support) [61] will be implemented.

#### Feasibility and Usefulness

The intervention’s feasibility for older adults will be assessed quantitatively based on the adherence rate (number of completed activity tandems and group meetings) during the intervention period. Additionally, participants will be given their own documentation sheet to record their subjective well-being (using a 5-level smiley scale at the beginning, middle, and end of each session) and their level of satisfaction (using a 5-point Likert scale) with each activity tandem meeting. Additional self-administered questionnaires with items to subjectively rate the activity tandem’s components will be implemented after every fourth unit. Using a 3-point Likert scale, participants will rate the difficulty of the particular intervention content (eg, strength, endurance, and coordination). In addition, they will be able to use the open response section to indicate which parameters they want to improve and what they want to achieve over the next 4 weeks. Six months into, at the end, and 6 months after the end of the intervention, participants will receive another self-administered questionnaire to assess the intervention’s feasibility and sustainability and to identify the optimizing factors of the activity tandems and group meetings.

To evaluate the feasibility of volunteer mentors and the communal context, (1) mentor workshops will be anonymously evaluated using a self-administered questionnaire, and (2) mentors and community project partner representatives will be asked to fill out a self-administered questionnaire (eg, questions on perceived feasibility and sustainability).

#### Implementation

To assess the implementation of the PA intervention, (1) self-administered questionnaires and (2) qualitative interviews will be conducted with mentors, participants, and community project partner representatives.

### Data Management

Participant information will be recorded using an individual identification code. All hard copies will be stored at Chemnitz University of Technology in locked cabinets accessible only to project staff members. Electronic data will be stored on a secured, password-protected computer. The databases will not contain participant identifiers. The data linking participant identifiers and the individual identification codes will be stored separately. Data quality will be ensured through double data entry and range checks for data values. Only project staff members will have access to the final trial data set.

### Statistical Analysis

SPSS Statistics (version 29; IBM Corp) and AMOS (version 29; IBM Corp) will be used for all quantitative statistical analyses. To determine the primary outcome at baseline (T1), the study population will be descriptively characterized using the following outcomes: demographics (eg, age, gender, family status, and income), anthropometric comorbidities, PA and health-related behavior (eg, smoking status and alcohol consumption), as well as physical, functional, cognitive, and psychosocial health status. Furthermore, participants’ data at the end of the intervention period (T2) and 6 months after its end (T3) will be analyzed to evaluate the long-term impacts, feasibility, and usefulness of the PA intervention. Time effects, group differences (eg, age, gender, vulnerability, and sociodemographic conditions) in terms of physical, cognitive, and psychosocial health, interaction effects, as well as the intervention’s feasibility and sustainability, will be analyzed using different parametric or nonparametric statistical methods such as the *t* test, Mann-Whitney *U* test, ANOVA, or Kruskal-Wallis test, depending on the number and size of the group, normal distribution, and homoscedasticity of the sample. Based on current evidence [6-8,25], associations and the strength of the relationship between 2 variables (eg, PA behavior and monthly income and adherence rate and level of education), correlation and regression analyses as well as adjustments for relevant covariates (eg, age, gender, and vulnerable criterion) will be performed. Additionally, multilevel analyses are planned to estimate, for example, the within-person impacts of the intervention program (eg, the impact of PA on well-being).

Qualitative interviews and focus group discussions will be protocolized by researchers and audio recorded, which will be transcribed afterwards. Qualitative data will be analyzed using a qualitative content analysis, according to Mayring and Fenzl [62], with the aim of structured processing of the material by coding relevant interview passages deductively in a theory-driven system of categories. Frequent text material that cannot be assigned to a deductive main category will result in the creation of new (inductive) main categories or subcategories [62]. The coding scheme will subsequently be supplemented with additional categories that emerge from the text material. These newly added categories will either be treated as subcategories of already existing categories or as new main categories. The text material will be coded with the help of MAXQDA (VERBI GmbH).

For this pilot study in the municipal area, the number of participants was calculated based on the project period and the project funding type in terms of feasibility within the study period.

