### Design and Organization of a Physical Activity–Promoting Intervention

All participants will participate in the target group-specific community-based PA intervention. The pilot study’s intervention period is 12 months per participating neighborhood. The participants will be encouraged to continue to engage in PA independently (Figure 2).

The intervention’s main component will comprise regular PA meetings organized in so-called “activity tandems,” which take place once a week for 30-45 minutes. One activity tandem will include 1 trained voluntary mentor and 3-4 older adults living in the same neighborhood. These activity tandems will primarily engage in low-threshold outdoor PA and exercise together in their neighborhood. For this, easily accessible locations such as urban lawns, walking paths, parks, and fitness trails will be used. In case of bad weather, the PA meetings will be organized in the meeting places of collaborating partners, for example, community centers. Due to the small group size, the content of each tandem lesson can be flexible and tailored to the individual participant’s needs. For example, the exercises can be performed at different levels of intensity, or alternative exercises can be selected from a large PA-exercise pool. Additionally, monthly group meetings (eg, 3-4 activity tandems with a total of 12-16 older adults) will be organized in each neighborhood district in the intervention months 5-12 (Figure 2), which will be delivered by trained exercise instructors. In these group meetings, in addition to PA exercises, the following contents will be covered: knowledge about the positive effects of PA, goal setting and planning, barrier management, and motivational aspects, as well as the sustainable implementation of regular PA in everyday life. Measures like small group sizes, qualified mentors, support material (eg, first aid kits, pulse oximeters, Borg scales), and the accessible, familiar environment of the activity sessions ensure the safety and well-being of participating older adults.

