### Measures

All participants will complete an assessment at baseline (T1), at the end of the 12-month intervention (T2), and 6 months after the end of the intervention (T3). Before each assessment, participants will be asked to fill out a self-administered questionnaire and, for the detection of objective PA behavior, will be given a pedometer to wear for 7 consecutive days. The questionnaire will assess the older adults’ psychosocial and physical health and evaluate motivational aspects related to PA in a community setting. Sociodemographic information will be assessed within the questionnaire at T1 only, comprising target group-specific items from the German Health Interview and Examination Survey for Adults [49].

Further measurements will take place in communal facilities in the older adults’ neighborhood and will be carried out by qualified staff members. Each assessment will start with the measurement of anthropometric data (height and weight) as well as the registration of current medication intake and existing diagnosed diseases via interview. Using the EQ-5D-3L questionnaire, the participants’ subjectively perceived health status in terms of mobility, self-care, regular daily activities, pain, discomfort, anxiety, and depression will then be determined by interview (3 response options: no problems, some problems, and serious problems) [50]. Additionally, their general self-rated health status will be recorded using the vertical visual analog scale EQ-VAS (1-100) [50].

An additional process evaluation will be performed during the intervention period using questionnaires for participants (after a period of 4 weeks) and mentors (after the workshop, 3 months after the intervention). Furthermore, qualitative interviews and informal notes, reports, and documentation of the PA groups will also be obtained from the activity tandems as well as from group meetings (Table 1 for a summary of outcomes).

**Table 1 table1:** Outcome measurements of the population-based prospective observational cohort study BeTaSen (Bewegungs-Tandems in den Lebenswelten Chemnitzer Seniorinnen und Senioren: ein Beitrag zur kommunalen Gesundheitsförderung). T1 is baseline, T2 is the end of the intervention period (12 months), and T3 is 6 months after the end of the intervention (study population: older adults aged 75 years or older living in Chemnitz, Germany).

Assessment		Instrument or scale	Time of measurement	
**Outcome**				T1, T2, T3

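### The rule for choosing tests of change over time ignores pairing, and the only rank tests it names are for independent groups

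*Protocol article*

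**What the plan says.** The study has one group and no control: "All participants will participate in the target group-specific community-based PA intervention" (Design and Organization of a Physical Activity–Promoting Intervention). The same people are measured three times (Measures), the last time half a year after the programme finishes: "All participants will complete an assessment at baseline (T1), at the end of the 12-month intervention (T2), and 6 months after the end of the" […].

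The Statistical Analysis section covers several aims in one sentence. It lists "Time effects, group differences (eg, age, gender, vulnerability, and sociodemographic conditions) in terms of physical, cognitive, and psychosocial health, interaction effects", together with feasibility and sustainability, and refers them all to "different parametric or nonparametric statistical methods such as the" t test, the Mann-Whitney U test, "ANOVA, or Kruskal-Wallis test, depending on the number and size of the group, normal distribution, and homoscedasticity of the sample".

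The same section later adds that "multilevel analyses are planned to estimate, for example, the within-person impacts of the intervention program", with the effect of physical activity on well-being as the example.

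**The concern.** Mann-Whitney and Kruskal-Wallis assume independent samples. With a single cohort, a comparison of T1 with T2 or T3 is always a comparison of people with themselves. The section gives a rule for choosing a test, but the rule does not ask whether the data are paired. Followed as written for an outcome that fails the normality check, it leads to an independent-groups rank test on repeated data. This could well happen with bounded scores such as the SPPB (0 to 12) or the MoCA.

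The first research question asks about long-term outcomes after the programme, and the Discussion defends the uncontrolled design by what it can show within persons. A test that is too conservative can leave a real gain or a real decline undetected. Because the Discussion expects outcomes to increase or be maintained, an undetected decline could be read as maintenance. Sample size was set by project period and funding, so no power calculation guards against lost precision.

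The second research question, on group differences in long-term outcomes, raises a related gap. Applied to the outcome values themselves, neither named rank test can test a time-by-group interaction.

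**Working it through.** **What the rule takes into account.** The criteria are "depending on the number and size of the group, normal distribution, and homoscedasticity of the sample". Pairing is absent. No paired or repeated-measures procedure is named explicitly; the t test and ANOVA could be meant in those forms, but the two rank tests could not.

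**Inputs.** From the documents: about 120 participants planned, 86 recruited at submission, one group, three visits. The documents give no alpha, power, effect size, SD or within-person correlation, so there is no stated figure to reproduce. Assumed here: two-sided alpha 0.05, equal SDs across visits, correlation r between visits from 0.3 to 0.8, and no dropout.

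**Formulas, in SD units, for two visits and n people.**
- Correct paired SE = √(2(1−r)/n)
- Independent-groups SE = √(2/n)
- Ratio = 1/√(1−r)
- True type I error of the independent test = 2Φ(−1.96/√(1−r))
- Power of the independent test = Φ((d − 1.96·SE_ind)/SE_paired)

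**Example, n = 120, r = 0.5.** SE_paired = √(1/120) = 0.0913 and SE_ind = √(2/120) = 0.1291, a ratio of 1.41. A paired test has 80% power at d = 2.80 × 0.0913 = 0.256. The independent test then has power Φ((0.256 − 1.96 × 0.1291)/0.0913) = 51%. Its true type I error is 2Φ(−2.77) = 0.56%.

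| r | SE ratio | True type I error (nominal 5%) | d giving 80% paired power, n = 120 | Power of independent test |
|---|---|---|---|---|
| 0.3 | 1.20 | 1.9% | 0.303 | 68% |
| 0.5 | 1.41 | 0.56% | 0.256 | 51% |
| 0.7 | 1.83 | 0.03% | 0.198 | 22% |
| 0.8 | 2.24 | below 0.01% | 0.162 | 6% |

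The last column does not depend on n, because d scales with the paired SE.

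**Check on the rank tests themselves.** The formulas are for mean differences. A simulation with skewed (lognormal) outcomes, n = 120, 3,000 data sets per setting and the same shifts (at T2, and equally at T3 for the three-visit tests) gave these powers:

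| r | Mann-Whitney | Signed-rank | Kruskal-Wallis | Friedman |
|---|---|---|---|---|
| 0.3 | 65% | 74% | 65% | 69% |
| 0.5 | 47% | 73% | 43% | 67% |
| 0.7 | 20% | 73% | 13% | 68% |
| 0.8 | 6% | 72% | 2% | 68% |

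With no true change, Mann-Whitney rejected in 2.1%, 0.7%, 0.07% and 0% of data sets at these four correlations. The signed-rank test stayed between 4.4% and 5.6%. Results for n = 86 were almost the same.

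**Dependence on effect size.** From the formulas with n = 120 and r = 0.7, a 0.2 SD change gives 81% paired power against 23% for the independent test. A 0.3 SD change gives 99% against 75%.

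**The case against.** The strongest reply is that the text does not commit to the error. The list is illustrative and serves several aims, and for group differences Mann-Whitney and Kruskal-Wallis are appropriate. The t test and ANOVA have paired, repeated-measures and mixed forms. A multilevel analysis of within-person effects is planned in the same section; that family respects pairing and can carry visit-by-group terms. A Mann-Whitney test on individual change scores would also address an interaction between two visits and two groups, although the article does not mention change scores. Finally, the article may leave the paired variant and the model terms to an analysis plan that is not shown.

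Much of this stands. A reader might infer that within-person change in non-normal outcomes will be tested with the wrong standard error, or that no valid method for change is planned. The documents support neither: the list is open, and multilevel models are planned. A reader might also infer that most of the power would be lost. That holds only for small shifts with a correlation of about 0.7 or more, and the documents give neither quantity.

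The reply does not remove the point. On time effects the article does not stay silent and defer: it names tests and a rule for choosing among them, and the rule omits the one criterion that matters for repeated measurements. The multilevel models are an addition whose scope is given only by example, so they are not designated as the analysis of change.

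**Conclusion.** The point holds as a defect of wording with a calculable risk. If the named rank tests are applied as written to T1/T2/T3 change, the SE is too large by 1/√(1−r) and the test is conservative. The power loss runs from modest at r = 0.3 (80% to 68%) to most of the power for small shifts at r of about 0.7 or more (80% to 22% at 0.7). These figures rest on assumed correlations, equal SDs, a 5% two-sided level and shifts chosen to give the paired test 80% power. They are a range, not a prediction for this study.

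The error would be conservative, the list is open, and this is a pilot. The wording should be corrected before the T2 and T3 data are analysed, but the point falls short of a must-fix.

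**What to change.** Reword the Statistical Analysis section so that the method follows from the data structure:

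- Make the multilevel (mixed) model already planned the main analysis of change for all outcomes measured at T1, T2 and T3. Give it visit as a fixed factor, a participant random intercept and all available visits. Add group and visit-by-group terms for the second research question.
- Where a rank test of time effects is wanted, name Wilcoxon signed-rank for two visits and Friedman for three.
- Restrict Mann-Whitney and Kruskal-Wallis to between-person comparisons.

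The cost is a few sentences. The software already named has a mixed-model procedure, and neither data collection nor sample size changes.

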## Introduction

### Overview

The share of older adults in many European countries’ total population is increasing [1]. Aging is associated with a number of physical and health-related changes, including a decline in physical and cognitive performance and an increase in neurodegenerative as well as cardiovascular diseases [2]. Furthermore, demographic developments and age-related increases in individual disease risk pose significant (health-related) economic and social challenges for aging societies. This manifests itself in increased hospitalizations [3] and financial burdens on both the health care system and private households due to rising health care costs [4]. Thus, healthy aging, for example, years of life spent in good health and the maintenance of well-being in old age, has enhanced attention in social and health systems [2]; investments in and programs to promote health are increasing in importance. According to current research, vulnerability in older adults (eg, poverty, loneliness, and a low level of education) can adversely affect the health behavior, morbidity, and mortality of older adults [5-9]. German adults with an income of less than 60% of the national average, for example, have a significantly reduced life expectancy compared to those with above-average incomes [8]. Consequently, it is crucial to focus, especially on these target groups, on health promotion programs.

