### Inclusion and Exclusion Criteria

The study primarily targets older adults aged 75 years or older who can be considered vulnerable (eg, poverty, loneliness, physical restrictions, and a low level of education) and who reside in the city of Chemnitz.

Residents are eligible to participate in the study if they (1) have at least basic knowledge of the German language, (2) can independently travel to the assessment and intervention locations, which will be meeting points in close proximity to their home, and (3) provide informed consent to participate in the study.

Participants will be excluded from the study if they have a medical condition preventing them from engaging in regular PA or if they had a severe adverse health event within the last 6 months (eg, myocardial infarction, stroke, fracture, surgery, or pneumonia) to ensure their safety during the PA sessions. Additionally, participants will be excluded if they participate in other clinical trials as well as in regular PA programs at least twice a week (eg, regular gym visits or rehabilitation exercise programs) to address older adults who are less physically active and to analyze solely the impact of the intervention.

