In line with previous literature and findings, the vulnerable target group’s potential barriers should be carefully considered when developing the pilot study. To ensure low-threshold accessibility, the activity tandems and monthly group meetings will take place in the older adults’ neighborhoods. District plans will be drawn up to identify sitting areas and public toilets, for example, and to pinpoint accessible walkway plans. The activity tandem’s PA content will be designed to reflect daily life activities in a very playful, individualized, ability-oriented, and motivational way. Each unit can be freely designed by the mentors and older adults based on the PA, exercise materials, and recommendations provided. Each activity tandem unit should begin with a warm-up, and the components of strength, endurance, coordination, stretching, and relaxation should be addressed regularly in different sessions. In addition, the mentor should include knowledge transfer in each unit, for example, about the positive effects of PA. Moreover, participation in the PA intervention does not entail any financial costs (eg, materials and participation fees). To promote sustainable participation in the neighborhood meetings and to ensure that the PA meetings are tailored to the vulnerable target group, the activity tandems are purposely organized for a smaller number of older adults. The older adults and mentors of the activity tandems can coordinate the time and location of their weekly meetings flexibly on their own.

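### The example covariate 'vulnerable criterion' overlaps by definition with the example exposures income and education, so adjusting for it can remove part or all of the association or reverse it

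*Protocol article*

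**What the plan says.** The Statistical Analysis section plans correlation and regression analyses of pairs of variables, with two illustrations: "eg, PA behavior and monthly income and adherence rate and level of education". The same sentence continues that "adjustments for relevant covariates (eg, age, gender, and vulnerable criterion) will be performed".

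The components of vulnerability appear elsewhere. The Inclusion and Exclusion Criteria target people "who can be considered vulnerable (eg, poverty, loneliness, physical restrictions, and a low level of education"), and the Introduction speaks of "vulnerability in older adults (eg, poverty, loneliness, and a low level of education"). Neither place gives thresholds, a scoring rule or a coding.

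The Statistical Analysis section also lists vulnerability as a grouping factor: "group differences (eg, age, gender, vulnerability, and sociodemographic conditions"). The authors thus seem to expect it to differ between participants. About 120 people are planned, a number set by project period and funding.

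**The concern.** Low income is close to poverty, and low education is itself a vulnerability marker. Adjusting the income or education association for a criterion built from these items means adjusting an exposure for a coarse copy of itself, mixed with other markers. The coefficient then answers a different question: how activity varies with income among people at the same level of vulnerability.

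This has two effects.

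- Part of the exposure's own contrast is absorbed by the covariate.
- Holding an any-of-these criterion fixed ties the markers together. Someone who is vulnerable but not low-educated must be poor, lonely or physically restricted. If those traits also lower activity or adherence, the better-educated look worse for that reason.

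A real social gradient could then be reported as weaker than it is, absent or reversed. The study asks about group differences by vulnerability (Research Objectives and Research Questions) and wants to inform programs for disadvantaged older adults, so such a result could mislead.

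**Working it through.** The article gives no coefficient, coding, prevalence or effect size for these associations, so there is no stated figure to reproduce. All inputs below are assumptions, used to see how far the result can move.

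**Inputs.** Four markers (poverty, low education, loneliness, physical restriction), each present in p = 20%, 30% or 40%. Outcome in SD units: income +0.15 per SD, low education -0.20, loneliness -0.2 or -0.3, restriction -0.3, -0.5 or -0.8. Poverty is the lowest p of a normal income distribution, so the poor differ from the rest by -0.15 × φ(z)/(p(1-p)). At p = 0.30 this is -0.15 × 0.3477/0.21 = -0.248.

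**1. Any-of-four flag, independent markers.** People without the flag show no variation in education, so the adjusted coefficient comes from flagged people only. There, each other marker has prevalence p among the low-educated and p/(1-(1-p)³) among the rest. With B the sum of the other three effects:

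adjusted effect = -0.20 + B × [p - p/(1-(1-p)³)]

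- p = 0.30, restriction -0.8, loneliness -0.2: B = -1.248; bracket = 0.30 - 0.30/0.657 = -0.157; result -0.20 + 0.195 = about -0.005.
- Mildest case (p = 0.40, restriction -0.3, loneliness -0.2): B = -0.7415; bracket = 0.40 - 0.40/0.784 = -0.110; result -0.118, a loss of 41%.
- Strongest case (p = 0.20, restriction -0.8, loneliness -0.3): B = -1.3625; bracket = 0.20 - 0.20/0.488 = -0.210; result +0.086, a loss of 143%.

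Simulation gives the same range. The income slope falls from 0.15 to 0.08-0.12.

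**2. Count of four, independent markers.** The adjusted effect is -0.20 - B/3. At p = 0.30 with restriction -0.8 and loneliness -0.2, this is -0.20 + 0.416 = +0.216. With restriction -0.3 it is -0.20 + 0.748/3 = +0.049. The sign reverses in all 18 scenarios.

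**3. Poverty flag in the income model.** Share of income variance explained: φ(z)²/(p(1-p)) = 0.576 at p = 0.30. Variance inflation is 1/(1-0.576) = 2.36, so the standard error is multiplied by √2.36 = 1.54. If the outcome is linear in income, 99-101% of the slope remains. If income acts only through the poverty threshold, about 0% remains.

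**4. Correlated markers (0.3), any-of-four flag.** The education coefficient is -0.07 to -0.22. That is close to the built-in -0.20 in some scenarios, but well below the unadjusted slopes of -0.36 to -0.48, which also carry the other markers' effects. At p = 0.30 with restriction -0.8 and loneliness -0.3, education is -0.147 and income 0.154.

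**5. Everyone meets a yes/no criterion.** The covariate is constant and the adjustment changes nothing.

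**Scale.** With 120 participants, p = 0.30 and residual SD 1, the standard error of the education effect is about 1/√(120 × 0.3 × 0.7) = 0.20 SD. In case 1 the shift is 0.08 to 0.29 SD, roughly 0.4 to 1.4 standard errors.

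**The case against.** The strongest reply is that the text fixes no such model. The variable pairs, the covariates and the vulnerability markers are each introduced as examples, and the covariates are called relevant ones. Covariate sets per model and the coding of the criterion are commonly left to a fuller document. This stands in part: the missing coding is not itself a fault, and a reader should not infer that the income and education models are certain to contain this covariate. But the article does illustrate the adjustment in the same sentence as the two exposures, and nothing says that the overlapping component is left out.

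Second, a reader might infer that the adjusted coefficients must lose most or all of the association. The working does not support that. The loss runs from almost none to sign reversal, and the most striking figures rest on independent markers, which is unlikely for income, education, loneliness and restriction. In the other direction, the income slope survives an any-of-four flag untouched when only income affects the outcome, and that sits badly with the Introduction, which links low education and physical restrictions to lower activity.

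Third, in a cohort where everyone is vulnerable the covariate is inert. That is right. With independent markers the education coefficient in such a cohort matches the flag-adjusted one, but that comes from eligibility, and changing the covariate would not cure it.

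Fourth, replacing the composite by all the other markers is no neutral repair. Loneliness and physical restriction may lie on the path from income or education to activity. This stands, and the fix below reflects it. That such a model recovers the simulated effects proves little, because the outcome was generated from those same terms.

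**Conclusion.** The point holds in a limited form. The covariate named as an example overlaps by definition with both exposures named as examples, and adjusting for it can shrink, remove or reverse the association. The size cannot be fixed from the article. Under the assumed inputs, a low-education effect of -0.20 SD moves to between -0.12 and +0.09 with a flag and independent markers, becomes positive with a count, and lies between -0.07 and -0.22 with a flag and markers correlated at 0.3. With a poverty flag and a linear income effect, almost nothing changes except precision.

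The weight is modest. These analyses are exploratory, and they are not the only relationships the section names: it also mentions activity and well-being in the multilevel analysis. Nor would they show whom the program fails to reach, since only enrolled people contribute data. The main questions on long-term outcomes and feasibility do not rest on them. The reason to act is that the stated adjustment can give a misleading answer and is easy to correct.

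**What to change.** In the Statistical Analysis section, state that the composite vulnerable criterion is not used as a covariate in any model whose exposure is one of its components (income or poverty, education). Adjust those models for age and gender, and report the unadjusted estimate beside the adjusted one.

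A model that also enters the other vulnerability markers as separate baseline variables can be added as a sensitivity analysis. It should be labelled as such, because some of those markers may be mediators.

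The cost is a change of wording and a little extra analysis. No new data appear to be needed: income is already part of the planned baseline description, and sociodemographic items are collected at T1. The sensitivity model spends a few more terms on a sample of about 120. The change does not address selection into a cohort defined by vulnerability, which belongs in the interpretation.
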